### 2.7. Instruments

The outcome measures include a wide range of tests and batteries focusing on cognitive state, body composition, sarcopenia, cardiovascular state, physical fitness, lifestyle, frailty, emotional state, satisfaction with life, and motivation [54,55,56,57,58,59,60,61,62,63,64,65,66,67,68,69,70,71,72,73,74]. The dimensions, tests, and their description are provided in Table 3.

### 2.8. Procedures

The participants will be evaluated at the Department of Sport Science within the University of Almeria by the same researchers, the week before (pre-test) and after (post-test) the 18-week training program. In addition, the participants will be assessed at 3- and 6-month post-intervention (re-test 1 and re-test 2, respectively) to examine the sustainability of any observed benefits across different outcome domains. Each participant will be required for two days of evaluations, each day for a duration of 60 min. Evaluations will be performed between 08:30 and 13:45, with the laboratory temperature normalized to 24 °C.

On the first day of assessments, the participants will be assessed in the following order: body composition and anthropometry variables, flexibility test (sit-and-reach test and back scratch test), cardiovascular state (blood pressure and resting heart rate), SPPB battery (chair stand test (CST), 4-m walk test (4MWT), and balance test), handgrip test, and 6-minute walk test. During the second day, participants will complete the following: sociodemographic questionnaire, psychosocial tests (CESD-R, PSQ, EQ-i-M20, SWL, and BREQ-3), physical activity questionnaire (IPAQ-S), Fried questionnaire, cognitive tests (VST and TMT test), 10-m walk test (10MWT), timed up and go test (TUG), and upper and lower limbs muscle strength.

### 2.9. Statistical Analysis

The qualitative data from sociodemographic questionnaires will be summarized using frequencies, while the rest of the quantitative variables will be described using the mean and SD for both the TG and CG across different assessment time points. To ensure robust statistical evaluation, Type I (alpha) error control will be prioritized, with the Bonferroni correction applied to set the threshold for statistical significance at *p* = 0.05. Group comparisons will adhere to the intention-to-treat principle, incorporating necessary adjustments for adherence to the exercise program. Missing data will be handled using multiple imputation based on fully conditional specification (FCS), performed in SPSS 25.0 using the Multiple Imputation module.

To assess baseline characteristic differences between groups, the Student’s *t*-test will be used for parametric numerical variables, the Mann–Whitney U test for non-parametric variables, and the chi-square (χ^2^) test for categorical binary variables. Changes within and between the TG and CG from baseline to follow-up assessments will be analyzed using the appropriate tests. For variables with a normal distribution, a repeated-measures analysis of variance (ANOVA) will be applied. Post hoc comparisons will utilize *t*-tests with Sidak corrections to control Type I errors. For non-parametric variables, the Friedman test will be followed by the Wilcoxon test, with the Bonferroni correction applied for multiple comparisons. Sensitivity analyses will be conducted to assess the robustness of the main results under varying assumptions, including analyses with and without imputed datasets and potential alternative modeling strategies.

All statistical analyses will be conducted using SPSS version 25.0. A *p*-value of <0.05 will indicate statistical significance, with adjustments made for multiple comparisons as described above.

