Primary evaluations	Sociodemographic questionnaire	Ad hoc	An ad hoc questionnaire used in previous research [1] will be used to collect data on age, sex, physical independence, history of chronic diseases, and systematic exercise.
	Cognitive state	Victoria Stroop Test (VST)	The Stroop test assesses attention, inhibition, and processing speed, observing the Stroop effect where reading interferes with color identification. The test involves three phases and aims to distinguish between colors and words accurately without errors [2].
		Trail Making Test (TMT)	TMT test assesses thought flexibility and visuospatial ability. It involves connecting numbers and words in a numerical sequence without making errors.
	Body composition and anthropometric variables	Bioimpedance + Anthropometry variables + Proportionality variables	Regarding body composition, fat mass, fat-free mass, lean mass, and muscle mass will be assessed with Inbody 120. The measurements shall be carried out according to the manufacturer’s standardization conditions and previous studies [3]. Body mass, with Inbody 120; height with SECA 217 scale; and waist and hips with Lufkin tape; will be assessed according to the guidelines of the International Society for the Advancement of Anthropometry (ISAK) [4]. Subsequently, BMI (kg/m^2^), as well as waist/hip and waist/height ratio, will be calculated [5]
	Sarcopenia	Handgrip test and chair stand test (CST) (5-times sit-to-stand)	The probability of sarcopenia will be assessed using the handgrip test with a Takei tkk5401 dynamometer (P & A Medical Ltd., Duxbury, UK) and CST (5 times sit-to-stand), following the indications of the European consensus on definition and diagnosis [6]. The tests will be performed according to the protocol of previous research [7].
		Muscle mass	For the diagnosis of sarcopenia, muscle mass will be assessed using Inbody 120, following the indications of the European consensus on definition and diagnosis [6]. The tests will be performed according to the protocol of previous research [3].

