		Timed Up and Go test (TUG) + Gait speed test (4 m walk test—4MWT) + Short Physical Performance Battery (SPPB)	The severity of sarcopenia (functional performance) will be assessed using TUG, gait speed, and the SPPB test, following the indications of the European consensus on definition and diagnosis [6]. The tests will be performed according to the protocol of previous research [7]. Photovoltaic cells from Microgate (Bolzano, Italy) will be used for TUG and 4MWT. The SPPB battery includes the balance test, gait speed test, and chair stand test. The Total SPPB score, ranging from 0 to 12, will be calculated by adding the scores from the three individual tests, following previous studies [8].
	Cardiovascular state	Blood pressure and resting heart rate	Blood pressure and resting heart rate will be measured using a calibrated and automated device (Omron M6W, Omron Healthcare Ltd. Hoffman Estates, IL, USA), following the protocol of previous studies [9]
	Physical fitness	Upper and lower limbs muscle strength	Upper and lower limb isometric muscle strength will be evaluated using the functional electromechanical dynamometer Dinasystem. For this purpose, the following exercises will be performed randomly, maintaining the isometric phase for 6 s during evaluation: bilateral rowing; bilateral push from the seated position with shoulder abduction at 45° and elbow flexion at 90°; and the sit-to-stand test. All of this will follow the methodology of previous research [10].
		Velocity	The 10 m walk test (10MWT) will be used for the assessment of velocity. Photovoltaic cells from Microgate (Bolzano, Italy) will be used for evaluation. This test will be conducted following the guidelines of previous research [11].
		Cardiorespiratory fitness	The 6-minute walk test will be used for the assessment of cardiorespiratory fitness. The distance covered, heart rate at the end, and heart rate recovery at 1 and 3 min will be recorded, following previous studies [12].
		Flexibility	Sit-and-reach test with a box (Acuflex, Psymtec, Madrid, Spain) and back scratch test will be used for the assessment of flexibility, following the protocol of previous studies [13]
Secondary evaluations	Physical activity (PA)	International Physical Activity Questionnaire (IPAQ-SF)	The short version of the IPAQ-SF for adults will be used to analyze levels of PA [14]

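### Type I error control is claimed through Bonferroni at p = 0.05, but nothing described corrects across the five outcome dimensions that Table 3 labels primary

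*Protocol article*

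**What the plan says.** Section 2.9 (Statistical Analysis) states that "Type I (alpha) error control will be prioritized", "with the Bonferroni correction applied to set the threshold for statistical significance at *p* = 0.05". Two specific procedures follow. For normally distributed variables, after the repeated-measures ANOVA: "Post hoc comparisons will utilize *t*-tests with Sidak corrections to control Type I errors". For the others: "the Friedman test will be followed by the Wilcoxon test, with the Bonferroni correction applied for multiple comparisons". The section closes by saying that a p-"value of <0.05 will indicate statistical significance, with adjustments made for multiple comparisons as described above".

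Table 3 places cognitive state, body composition and anthropometry, sarcopenia, cardiovascular state and physical fitness in its primary block. Single rows hold several measures. For example: "Regarding body composition, fat mass, fat-free mass, lean mass, and muscle mass will be assessed with Inbody 120", and for the 6-minute walk: "The distance covered, heart rate at the end, and heart rate recovery at 1 and 3 min will be recorded". The same block opens with a sociodemographic form: "An ad hoc questionnaire used in previous research [1] will be used to collect data on age, sex".

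Section 2.3 sets the sample size at a 5% Type I error rate and 75% power, without naming the outcome that drives it. The Introduction calls the trial preliminary and exploratory, and also hypothesises significant improvements in cognitive, physical and psychological outcomes.

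**The concern.** Bonferroni over k tests compares each p-value with 0.05/k, or equivalently compares k times the p-value with 0.05. Either way, k and the family it counts must be stated for the correction to have any content. Here neither is given, and the literal sentence describes a threshold that equals the uncorrected one.

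The procedures that are spelled out deal with comparisons inside one variable's analysis. They do nothing about the number of variables, and Table 3 makes that number large for the primary block alone. A reader of the results would believe that Type I error had been protected across the primary outcomes, when each could be tested at 0.05. The article's stated cautions concern Type II error and generalisability (Sections 2.3 and 3). It nowhere warns of false positives from many primary measures.

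**Working it through.** **1. The stated threshold.** Bonferroni per-test level = 0.05/k. It equals 0.05 only for k = 1. For k = 11 it is 0.05/11 = 0.0045. For k = 30 it is 0.05/30 = 0.0017. The stated 0.05 is therefore not reproduced as a per-test level for any family larger than one.

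**2. Counting the primary block of Table 3** (sociodemographic form and height left out; each measure counted once, not once per visit):

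| Dimension | Test rows | Itemised measures |
|---|---|---|
| Cognitive state | 2 | Stroop, Trail Making = 2 |
| Body composition, anthropometry | 1 | 4 mass components; body mass, waist, hips, BMI, 2 ratios = 10 |
| Sarcopenia | 3 | handgrip, chair stand, TUG, gait speed, SPPB = 5 (muscle mass counted above) |
| Cardiovascular state | 1 | systolic, diastolic, resting heart rate = 3 |
| Physical fitness | 4 | 3 isometric tests, 10 m walk, 4 from the 6-minute walk, 2 flexibility = 10 |
| Total | 11 | 30 |

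Scoring the Stroop phases and Trail Making parts separately would raise the 30 to about 32 to 34.

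**3. Chance of at least one false positive if each is tested at 0.05 with no effect.** Under independence this is 1 − 0.95^k:
- k = 11: 1 − 0.95^11 = 0.431
- k = 30: 1 − 0.95^30 = 0.785, with 30 × 0.05 = 1.5 false positives expected

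These measures are correlated, and the documents give no correlations. Assuming a common correlation r between normal test statistics (simulation, 200,000 draws):

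| k | r = 0 | r = 0.3 | r = 0.5 | r = 0.7 |
|---|---|---|---|---|
| 11 | 43% | 38% | 30% | 22% |
| 30 | 79% | 66% | 51% | 34% |

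**4. What a real correction would cost at the planned size.** 26 per group less 15% leaves about 22 completers (22/0.85 = 25.9, rounded up to 26). Section 2.3 gives no effect size. A two-sample t-test with 22 per group, two-sided 0.05 and 75% power implies d of about 0.81. At that d and n, power is:
- at 0.05: 75%
- at 0.01 (first Holm step with one measure for each of five dimensions, 0.05/5): about 51%
- at 0.0045 (k = 11): about 39%
- at 0.0017 (k = 30): about 27%

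**The case against.** The strongest reply is that 0.05 may be the family-wise level, or the level to which adjusted p-values are compared. The closing sentence of Section 2.9, which pairs 0.05 with adjustments already described, fits that reading. It does stand against saying that a threshold of 0.05 can never be a correction. It does not rescue the claim, because the only adjustments described work within one variable. An unseen full protocol or SAP might define the family, but the article makes a positive claim of control that its own described procedures do not deliver.

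Several other points stand and limit the finding:
- The article calls the trial preliminary and exploratory and asks for cautious reading, so control across outcomes is not obligatory. The fault lies in claiming it.
- The count of 30 is an itemisation. The article does not say that each measure is a separate primary test. Several overlap: BMI tracks body mass, and SPPB contains the chair stand and gait speed. The independence figure of 79% is therefore an upper end.
- Section 2.8 gives the 3- and 6-month re-tests the role of examining whether benefits last, which points to post-test as the main assessment. The visits should not be counted as three co-equal primary time points.

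A reader might infer that a false primary success is more likely than not. That holds only for about 30 measures with correlation up to about 0.5. At 11 rows, or at a correlation of 0.7, it does not. A reader might also infer that the trial will be declared successful on any one significant measure. No such rule is written: the hypothesis joins cognitive, physical and psychological outcomes, and the psychological ones are secondary in Table 3.

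**Conclusion.** The point holds as a contradiction between a claim and the method described. Section 2.9 says Type I error control has priority, but defines no family and no k, and corrects only within variables. Across the outcomes labelled primary, error is not controlled as claimed.

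The false-positive chance of 22% to 79% rests on three assumptions: 11 to 30 tests, each at 0.05, and a common correlation between 0 and 0.7. Every case is at least four times the nominal 5%. The exploratory status makes removing the claim a legitimate repair, but it does not make the present sentence correct. The sociodemographic questionnaire in the primary block is a minor labelling fault.

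**What to change.** Replace the quoted sentence in Section 2.9 before the pre-test; Section 2.4 says baseline assessments have not started. Choose one of two forms.

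(a) Name one primary outcome at post-test, tested at two-sided 0.05. This matches the unadjusted 5% in Section 2.3. Make all other measures, and both re-tests, secondary or exploratory, reported as TG − CG differences with 95% confidence intervals. Cost: only one outcome can support a claim of significance, and the choice must be consistent with the registered outcome, which the article does not show.

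(b) Remove the claim of Type I error control across outcomes. Report all outcomes as estimates with 95% confidence intervals, and state that p-values are not adjusted across outcomes and support no confirmatory claim. Cost: the hypothesis of significant improvements in the Introduction needs softer wording.

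One measure per dimension under Holm is also possible. Its first step of 0.01 lowers power from 75% to about 51% at 22 completers per group (implied d about 0.81), and the protocol would have to say so.

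In every case, move the sociodemographic questionnaire out of the primary block of Table 3, and say that the Sidak and Bonferroni post hoc corrections apply within a variable. The change is to wording in Section 2.9 and Table 3, plus the Introduction under (b). Neither (a) nor (b) changes the sample size.

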### 2.3. Sample Size and Power Calculation

The sample size was calculated using RStudio 3.15.0 software (RStudio Inc., Boston, MA, USA) prior to the recruitment of participants. Assuming a study design with a 5% Type I error rate and 75% statistical power, the calculation was informed by effect sizes reported in similar multidomain interventions. These effect sizes were drawn from studies targeting physical, cognitive, and psycho-physiological outcomes in older adults [41,42,43]. A potential 15% dropout rate has been accounted for in the final estimate [44]. This yielded a total sample size of 52 participants (26 per group). While this sample size is considered sufficient to detect meaningful changes, the relatively small cohort may increase the risk of Type II errors. Therefore, upon completion of the trial, the results will have to be interpreted with caution and regarded as preliminary until validated by studies with larger samples.

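### Non-normal outcomes are to be multiply imputed and then tested by Friedman and Wilcoxon, which give no between-group estimate and standard error to pool

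*Protocol article*

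**What the plan says.** Section 2.9 of the protocol article fixes both how missing data are filled in and which tests follow.

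- Principle: "Group comparisons will adhere to the intention-to-treat principle, incorporating necessary adjustments for adherence to the exercise program".
- Missing data: "Missing data will be handled using multiple imputation based on fully conditional specification (FCS), performed in SPSS 25.0 using the Multiple Imputation module".
- Outcomes treated as normal: "For variables with a normal distribution, a repeated-measures analysis of variance (ANOVA) will be applied", and then "Post hoc comparisons will utilize *t*-tests with Sidak corrections to control Type I errors".
- Outcomes treated as non-normal: "For non-parametric variables, the Friedman test will be followed by the Wilcoxon test, with the Bonferroni correction applied for multiple comparisons".
- Sensitivity analyses: these are planned, "including analyses with and without imputed datasets and potential alternative modeling strategies".

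The section closes with one decision rule: significance at p below 0.05, after the stated multiplicity adjustments. Section 2.8 sets four assessments (pre-test, post-test, and re-tests at 3 and 6 months). Section 2.3 gives 52 participants, 26 per group, with 15% dropout allowed for.

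**The concern.** Multiple imputation produces m completed datasets. Its validity rests on analysing each one, taking an estimate and its standard error, and combining them so that the spread between datasets enters the final standard error. That step needs an estimate with a standard error.

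Friedman and Wilcoxon do not supply one. Friedman tests for change over time within a set of subjects. The Wilcoxon test that normally follows it compares pairs of visits within subjects. So the rank path gives neither a quantity that Rubin's rules can combine nor a comparison of the two arms. A plan with one p-value criterion then meets m p-values per outcome.

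The rank path need not be marginal. The Discussion (section 3) expects a possible ceiling effect in the cognitive outcomes, which Table 3 lists among the primary evaluations. Table 3 also includes the SPPB total, bounded from 0 to 12, and a depression score that is often skewed. Which outcomes will be classed as non-normal is not known in advance. For those that are, the conclusion could depend on how the m results are reduced to one.

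**Working it through.** **Step 1. What each named procedure returns.** The plan gives no figure on this point to reproduce, so the first check is on the procedures themselves.

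| Procedure in section 2.9 | Estimate with standard error? | Standard pooling |
|---|---|---|
| Repeated-measures ANOVA, group-by-time contrasts | Yes, with covariance matrix | Rubin's rules; D1 (multi-parameter Wald) for the joint test |
| Repeated-measures ANOVA, omnibus F | No | Not directly; replace by D1 on the contrasts |
| Post hoc t-tests (Sidak) | Yes, mean difference | Rubin's rules |
| Friedman | No | None; D2 approximates a pooled p-value |
| Wilcoxon | No | None |

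**Step 2. An illustrative trial.** Taken from section 2.3: 26 per arm and 15% lost, here lost after baseline. Taken from section 2.8: four visits. Assumed: normal data, correlation 0.6 between visits, true difference 0.5 SD after baseline, m = 5. Friedman was run on the four visits within the training group, and Wilcoxon on the training group's change from pre-test to post-test.

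| Imputed dataset | Interaction F (p) | Between-group change (SE) | Friedman chi-square (p) | Wilcoxon p |
|---|---|---|---|---|
| 1 | 0.63 (0.60) | 0.313 (0.268) | 5.86 (0.119) | 0.029 |
| 2 | 1.43 (0.24) | 0.341 (0.230) | 8.08 (0.044) | 0.0086 |
| 3 | 3.00 (0.033) | 0.626 (0.233) | 14.86 (0.0019) | 0.0005 |
| 4 | 1.71 (0.17) | 0.463 (0.233) | 13.34 (0.0040) | 0.0008 |
| 5 | 1.97 (0.12) | 0.399 (0.239) | 11.68 (0.0086) | 0.0010 |

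**Step 3. Pooling where there is an estimate.** Rubin's rules: T = W + (1 + 1/m)B, where W is the mean squared standard error and B the variance of the estimates.

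- Mean estimate = (0.313 + 0.341 + 0.626 + 0.463 + 0.399)/5 = 0.428.
- W = 0.0581 and B = 0.0155, so T = 0.0581 + 1.2 × 0.0155 = 0.0767 and SE = 0.277.
- D1 on the three group-by-time contrasts: F = 1.22 on 3 and 115 df, p = 0.31.

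The ANOVA path thus reduces to one estimate and one test.

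**Step 4. The rank path.** Friedman has no estimate to put into T. The D2 approximation combines the chi-squares w over k = 3 df: r = (1 + 1/m) × var(√w) = 1.2 × 0.352 = 0.423. Then D = [mean(w)/k − ((m + 1)/(m − 1))r]/(1 + r) = (10.764/3 − 1.5 × 0.423)/1.423 = 2.08, p = 0.13. The result is a single approximate p-value with no effect size. Four of the five datasets taken singly had p < 0.05.

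**Step 5. How often the datasets disagree.** Over 1000 simulated trials of this kind, at least one but not all of the five datasets reached p < 0.05 in 27.6% for Friedman and 25.2% for Wilcoxon. The Monte Carlo standard error is √(0.276 × 0.724/1000) = 0.014 for each, to three decimals. The interaction F disagreed in 32.9%, so disagreement is not peculiar to rank tests. What differs is that the ANOVA path has a standard way to resolve it.

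**The case against.** The strongest reply is that this is detail for the analysis plan. An article commonly leaves out the number of imputations and the combining rule, and nothing in section 2.9 says that pooling will be skipped. This is right as far as it goes: silence on those items is no finding. But the article itself chose both the imputation method and the rank tests. The point is that these two stated choices do not fit together.

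A second reply is that approximate pooling of test statistics exists, as step 4 shows. This stands too, and it rules out saying that no valid answer can be had. It yields only an approximate p-value, however, and no difference between arms.

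A third is that Friedman and paired Wilcoxon are within-subject tests, so pooling would not make them compare arms. That is true, but it strengthens the case for a model that does compare them.

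The planned analyses with and without imputed data, and the description of the results as preliminary, lower the stakes. They do not supply a way to combine.

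A reader might also infer that the plan inflates false positives. In a null simulation of a t-test on change (26 per arm, pre-post correlation 0.7, 15% missing, m = 5, 6000 runs), pooling gave 4.6% false positives. Using one completed dataset gave 8.2%, and taking any of five p-values below 0.05 gave 16.4%. The plan prescribes neither shortcut, and the test simulated is one that can be pooled. The figures show what misuse would cost, not what the plan does.

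**Conclusion.** The concern holds for outcomes treated as non-normal. Imputation under intention to treat is paired with tests that give no between-group estimate and standard error, so standard pooling does not apply and one p-value per imputed dataset remains. Under the assumptions of step 2, those p-values fell on both sides of 0.05 in about 25% to 28% of simulated trials. That rate depends on the assumed effect, correlation and number of imputations, and on applying the rank tests within the training group. It is an illustration, not a forecast for this trial.

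For outcomes treated as normal the matter is small: the contrasts and t-test differences can be pooled, and only the omnibus F should not be carried across imputations as it stands. It would be wrong to conclude that repeated-measures ANOVA cannot be pooled.

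Nor do the documents support reading the plan as one joint imputation of every measure at every visit, too large for 52 people. Section 2.9 does not say that all outcomes enter a single run. Table 3 says that BMI, the waist ratios and the SPPB total are calculated from their components.

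**What to change.** In section 2.9, state that the imputed intention-to-treat analysis of every outcome, normal or not, uses a model giving the training-minus-control difference and its standard error at each visit, pooled across imputations by Rubin's rules. If a joint group-by-time test is wanted, pool the contrasts (D1) rather than the omnibus F. Confine Friedman and Wilcoxon to the unimputed sensitivity analysis that is already planned. If a rank test is kept on imputed data, name the combining rule and accept that it gives no effect estimate.

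The cost is a few sentences and slightly more analysis work, with no new data. Section 2.4 says that baseline assessments have not begun, so the change can be made before any outcome is seen.

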### 2.5. Randomization and Blinding

Randomization was performed electronically using Microsoft Excel 2016 before the start of the program and pre/tests. An investigator not involved in participant recruitment conducted the randomization process following a randomization sequence (1:1). In addition, the examiners in charge of carrying out the evaluations will be blinded, and the participants will be instructed not to disclose the group to which they have been assigned to when the assessments are carried out.

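### Baseline significance tests between randomised arms cannot show comparability at 26 per arm; describe baseline instead and adjust outcome comparisons for baseline value, age and sex

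*Protocol article*

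**What the plan says.** Section 2.9 gives the purpose of the baseline tests as "To assess baseline characteristic differences between groups". It assigns Student's t-test to parametric numerical variables, Mann–Whitney to non-parametric ones and chi-square to binary ones. It then analyses change within and between arms by repeated-measures ANOVA with Sidak post hoc tests, or by Friedman followed by Wilcoxon. No baseline covariate is named. The one adjustment mentioned is for adherence, which arises after randomisation. Sensitivity analyses may use other models, which are not specified.

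Section 2.5 says of the allocation: "An investigator not involved in participant recruitment conducted the randomization process following a randomization sequence (1:1". It describes no stratification. On timing it says: "Randomization was performed electronically using Microsoft Excel 2016 before the start of the program and pre/tests".

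The sociodemographic questionnaire in Table 3 is used "to collect data on age, sex, physical independence, history of chronic diseases, and systematic exercise", so age and sex will be on file. Section 2.3 sets 26 participants per group. Section 2.4 says baseline assessments have not begun.

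**The concern.** A significance test asks whether two groups come from the same population. For characteristics fixed before a random allocation the answer is already known to be yes, so a small p-value can only be a chance finding.

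The question that matters is whether an observed imbalance in a prognostic variable is large enough to distort an outcome comparison. The p-value does not answer it. In a trial of this size the threshold for significance is so wide that a material imbalance can sit well inside it.

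Covariate adjustment is the tool that deals with such an imbalance, and the analyses named in Section 2.9 do not include it. At stake are the reading of the baseline table, the bias of outcome contrasts given the imbalance that actually occurs, and some precision in a small trial.

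**Working it through.** **Inputs.** From Section 2.3: alpha 5% (two-sided assumed), power 75%, 15% dropout, 26 per arm. Not in the article, and so assumed: the effect size, the number of baseline variables tested, and the baseline–follow-up correlation ρ.

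**The plan's own figure.** Section 2.3 gives no numerical effect size; it says only that "the calculation was informed by effect sizes reported in similar multidomain interventions". The 52 can therefore only be back-solved.
- Per arm: n = 2(1.960 + 0.674)²/d² = 13.88/d².
- At d = 0.8, n = 21.7, rounded up to 22. Then 22/0.85 = 25.9, rounded up to 26 per arm, or 52 in total.
- d = 0.75 would give 60 and d = 0.85 would give 48. An effect near 0.8 SD is thus implied, if the calculation was a two-sample comparison of means. It serves below only as a yardstick.

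**What a non-significant baseline test can hide.**
- The standard error of a standardised difference at 26 per arm is √(2/26) = 0.277.
- The largest non-significant difference is t(0.975, 50 df) × 0.277 = 2.009 × 0.277 = 0.557 SD, about 70% of the implied detectable effect (0.557/0.8).
- If Bonferroni over 50 tests applied (0.001 each), the limit would rise to 0.97 SD. Section 2.9 does not say whether its multiplicity adjustments cover the baseline tests.

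**How often chance produces such an imbalance.**
- P(|difference| ≥ 0.4 SD) = 2 × P(Z > 0.4/0.277) = 0.149.
- P(|difference| ≥ 0.557 SD) = 0.045.
- The remainder, 0.149 − 0.045 ≈ 0.105, is the share of variables expected to differ by 0.4 to 0.56 SD without being flagged. That is about 5 of 50.

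**Chance findings among k tests at 0.05, uncorrected and independent.**

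| k | Expected | P(at least one) |
|---|---|---|
| 20 | 1.0 | 0.64 |
| 40 | 2.0 | 0.87 |
| 50 | 2.5 | 0.92 |
| 60 | 3.0 | 0.95 |

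The count of about 50 comes from Table 3 (roughly 45–55, depending on subscales). The measures overlap, so independence is generous: with 50 tests, P(at least one) falls to 0.80 at pairwise correlation 0.3 and 0.62 at 0.5. The expected number stays at 2.5.

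**What an imbalance D in the outcome's own baseline does to the result** (D is training minus control; equal SDs at both times):
- Contrast of change: conditional bias (ρ − 1)D. At D = 0.55 this is −0.28 SD for ρ = 0.5 and −0.11 SD for ρ = 0.8.
- ANCOVA on the baseline value: about zero. In simulated trials with 26 per arm and an imbalance averaging 0.43 SD, the bias was within 0.01 SD of zero at ρ = 0.5, 0.7 and 0.8. The change contrast was off by −0.21, −0.12 and −0.09 SD.
- Standard error of the arm difference at ρ = 0.5, 0.7 and 0.8: ANCOVA 0.242, 0.201, 0.168; change score 0.277, 0.215, 0.176.

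**The case against.** **Change analysis already protects against much of this.** This stands. A constant effect of age or sex on the level of strength, muscle mass or walking cancels in the group-by-time contrast. A reader might infer that the baseline p-values are the plan's only safeguard; they are not. What remains is regression to the mean and any influence of age or sex on change itself.

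**The null is not true by design for every variable.** This also stands. Randomisation preceded the pre-tests, and participants know their arm, since Section 2.5 asks them not to disclose it. Effort-dependent or self-reported baselines could therefore truly differ. Section 2.4 also lists exclusions after randomisation, including one for low attendance that applies only to the training group; arms formed that way need not be exchangeable. The argument is strict only for fixed traits in everyone randomised. The article does not give detection of such differences as the purpose of the tests, and they would detect them poorly.

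**No misuse of the p-values is stated.** Correct. A reader might infer that significant differences will be reported as real and non-significant ones taken as proof of comparability. Section 2.9 ties no decision rule to the results, so neither can be asserted.

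**Power is the wrong measure of the screen.** A reader might quote the power to detect a true 0.4 SD difference (29%) as the chance of flagging a 0.4 SD imbalance. That mixes two quantities. An observed 0.4 SD difference gives t = 0.4/0.277 = 1.44, p about 0.15, and is never flagged. The 0.557 SD limit is the relevant figure.

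**Covariates may be listed in a document not shown.** Possible, so the missing covariate is weaker evidence than the stated tests. The article does commit itself to the tests and names its outcome methods, and Friedman and Wilcoxon take no covariate.

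**The trial is exploratory.** True, and deleting the baseline tests alone changes no treatment estimate. The adjustment would.

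**Conclusion.** The point holds as a defect in stated text with a modest but real consequence. For fixed traits the planned tests can yield only chance findings; for pre-test measures they are a weak check. At 26 per arm they leave imbalances up to about 0.56 SD unflagged, and roughly one variable in ten is expected to lie between 0.4 SD and that limit.

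Without covariate adjustment, a 0.55 SD imbalance in an outcome's own baseline shifts the change contrast by about −0.28 to −0.11 SD for ρ between 0.5 and 0.8. This bias is conditional on the imbalance that occurs; averaged over possible randomisations the contrast is unbiased. The trial is not invalidated.

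The 0.56 SD limit follows from the stated sample size and a two-sided 0.05 test. The 2.5 expected chance findings rest on a count of about 50 and on no multiplicity correction. The bias figures rest on the assumed correlations.

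**What to change.** In Section 2.9:

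1. Delete the baseline t, Mann–Whitney and chi-square tests. Show baseline values by arm descriptively.
2. State that between-arm comparisons at each follow-up adjust for the outcome's own baseline value plus age and sex, by ANCOVA or a mixed model, whatever the observed balance. Fixing the set in advance also prevents covariates being chosen on baseline p-values.
3. For skewed outcomes, name a transformed, rank-based or robust model that accepts these covariates, because Friedman and Wilcoxon do not.

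The cost is three degrees of freedom per model (baseline value, age, sex) and replacement of the non-parametric branch for between-arm comparisons, so it is somewhat more than a change of wording. No new data are needed. By the article's account the pre-tests have not begun, so the change can still be prespecified.
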